#### TABATA training

2.5.3

The TABATA training module has been tailored to the needs of secondary school students under psychological stress. To ensure accessibility and ease of implementation, the module consists of simple, easy to follow exercises. It includes eight different movements, performed in two rounds, with a total duration of 8 min. The detailed exercise routine is provided in Table 2.

**Table 2 tab2:** The content of TABATA training module.

Round 1	Movements	Round 2	Movements
0:00–0:20	Jumping jacks	0:00–0:20	Jumping jacks
0:20–0:30	Rest	0:20–0:30	Rest
0:30–0:50	High knees	0:30–0:50	High knees
0:50–1:00	Rest	0:50–1:00	Rest
1:00–1:20	Jumping lunges	1:00–1:20	Jumping lunges
1:20–1:30	Rest	1:20–1:30	Rest
1:30–1:50	Air squats	1:30–1:50	Air squats
1:50–2:00	Rest	1:50–2:00	Rest
2:00–2:20	Butt kicker	2:00–2:20	Butt kicker
2:20–2:30	Rest	2:20–2:30	Rest
2:30–2:50	Standing abs twist	2:30–2:50	Standing abs twist
2:50–3:00	Rest	2:50–3:00	Rest
3:00–3:20	Half Squat Jump	3:00–3:20	Half Squat Jump
3:20–3:30	Rest	3:20–3:30	Rest
3:30–3:50	Squat jump	3:30–3:50	Squat jump
3:50–4:00	Rest	3:50–4:00	Rest

To ensure consistency and safety of the intervention, physical education teachers participating in this study will receive systematically standardized training prior to the intervention. This training will be co-led by the principal investigator of the research team and a senior fitness coach, consisting of two sessions, each lasting 1 hour. Training will cover an overview of the overall research protocol; demonstration and correction methods for standard TABATA movements; intensity monitoring techniques based on heart rate and the Rating of Perceived Exertion (RPE) scale; safety guidelines; and adverse event recording procedures. Following training, teachers must pass a practical demonstration assessment to participate in the formal study. Additionally, teachers will receive a standardized set of TABATA training music tracks to ensure consistent movement tempo and rest intervals across all sessions. During the study implementation phase, the principal investigator will conduct random on-site observations to evaluate teachers’ adherence to the research protocol (including time management, intensity monitoring, and movement standardization), further ensuring intervention fidelity.

#### Relaxation and stretching for cooling down

2.5.4

Relaxation stretching is an essential component of post-exercise recovery (Peake, 2019). It effectively reduces muscle tension and fatigue, enhances circulation to facilitate lactic acid removal, and minimizes post-exercise muscle soreness. Additionally, it improves flexibility and joint mobility, helping to prevent injuries caused by muscle stiffness and muscular imbalances (Loh et al., 2022).

Stretching also optimizes muscle contraction patterns, increases movement efficiency, and promotes smoother, more coordinated motor function, which contributes to improved overall athletic performance (Zvetkova et al., 2023). When combined with deep breathing and slow, controlled movements, relaxation stretching fosters mental relaxation, reduces post-exercise anxiety, and promotes a sense of calm. Furthermore, it supports blood and lymphatic circulation, aiding in nutrient delivery, waste elimination, and the recovery of muscles and tissues (Jermaina et al., 2022).

Accordingly, each TABATA session will conclude with a 4-min relaxation and stretching routine.

#### Intensity monitoring

2.5.5

This study will employ a combined objective and subjective approach to monitor and evaluate exercise intensity. For objective monitoring, participants will wear heart rate monitoring wristbands (Huawei brand) during all TABATA training sessions to track real-time heart rate changes. For subjective assessment, participants will be instructed to self-report fatigue levels immediately after each session using a modified Borg RPE scale (0–10), with instructors conducting verbal interviews and recording responses.

#### Suspension and exit

2.5.6

If a participant experiences paleness, dizziness, shortness of breath, chest pain, or any indication of severe discomfort, the training session will be immediately suspended for evaluation by the instructor and school nurse. If a participant is unable to perform a movement correctly due to technical inexperience or temporary fatigue, the instructor will provide a scaled-down alternative movement to ensure they can maintain target heart rate and engagement within safe parameters, rather than ceasing exercise entirely.

### Attendance and adherence

2.6

Each training session will feature a paper attendance sheet where instructors will record student participation. Participants’ exercise adherence will be quantified through the following methods: (a) Actual exercise duration data exported from heart rate monitoring devices; (b) Instructors will document each student’s completion of TABATA sets; (c) RPE values collected after each training session. Absences or incomplete sessions will be noted with the reason.

### Data collection instruments and outcome measures

2.7

The primary and secondary outcomes are defined in Tables 3, 4.

**Table 3 tab3:** The primary outcomes of the study.

Primary outcome measures	Definition	Success threshold
Recruitment rate	Proportion of all students who meet the eligibility criteria and agree to enter the study	>70%
Retention rate	Proportion of students that in the TABATA training group complete the 8-week intervention	>80%
Adherence rate	Actual number of times participated	>70%
Data missing rate	Overall missing data rate	<10%

**Table 4 tab4:** The secondary outcomes of the study.

Secondary outcome measures	Measurement indicators
Stress score	Changes in DASS-21 stress scores pre and post intervention
Quality of Life	Change of score on validated quality of life questionnaires QLSCA pre and post intervention
Physical fitness performance	Changes of score on Physical Fitness Test for Chinese Secondary School Students pre and post intervention
Academic performance	Changes in academic performance ranking pre and post intervention
Acceptability	Qualitative evidence generated from focus group discussions with participants

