### Data analysis

2.9

The analysis will focus on obtaining descriptive statistics and confidence intervals for the variables. Participants will be characterized by means, standard deviations, and ranges for quantitative variables, as well as counts and proportions for categorical variables. Since this is a feasibility study primarily aimed at testing our ability to collect data, we will not use data interpolation to address any missing data. Based on the proposal for the pilot study, we have set the following feasibility goals: within 1 month, the intervention group and the control group will each recruit 20 to 30 participants; achieving a recruitment rate of over 70% in the TABATA intervention group; ensuring that more than 80% of students in the TABATA training group complete the 8-week intervention; having more than 70% of adherence rate; and maintaining an overall missing data rate of less than 10%.

All interviews will be recorded using an Apple mobile phone and transcribed verbatim, followed by manual proofreading using Flying Book of Notes software. To gain a comprehensive understanding of participants’ perceptions, an inductive analysis approach will be employed to identify broader themes (Azungah, 2018). Data will be analyzed using NVivo 12 qualitative analysis software to extract key themes related to feasibility and acceptability.

To enhance the credibility and reliability of the findings, researcher triangulation will be used to minimize researcher bias and strengthen the overall robustness of the study (Natow, 2020). First, one member of the research team will input the transcribed data into NVivo 12 and conduct initial coding in collaboration with another team member, merging codes to form preliminary themes. Next, two additional researchers will review the coding and refine the thematic structure for further integration.

Inter-rater reliability will be assessed by calculating the Kappa coefficient using NVivo 12. A Kappa value greater than 0.75 will be considered acceptable, indicating high consistency and data validity. Finally, all members of the research team will convene to finalize the themes related to the feasibility and acceptability of the TABATA training module.

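### Table 3 and section 2.9 state the primary feasibility criteria inconsistently, and no criterion measures retention in the control arm

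*Protocol article*

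**What the plan says.** Section 2.7 refers to Table 3 for the definitions of the primary outcomes, and the table sets a definition beside a success threshold for each. Section 2.9 restates the goals.

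- **Recruitment, >70%.** Table 3: "Proportion of all students who meet the eligibility criteria and agree to enter the study". Section 2.9: "achieving a recruitment rate of over 70% in the TABATA intervention group". Section 2.9 also sets a count target for both arms: "within 1 month, the intervention group and the control group will each recruit 20 to 30 participants".
- **Retention, >80%.** Table 3: "Proportion of students that in the TABATA training group complete the 8-week intervention". Section 2.9 has the same restriction: "ensuring that more than 80% of students in the TABATA training group complete the 8-week intervention".
- **Adherence, >70%.** Table 3: "Actual number of times participated". Section 2.6 says that adherence will be quantified by exercise duration from the heart-rate device, by completed sets ("Instructors will document each student’s completion of TABATA sets") and by the RPE values.
- **Missing data, <10%.** Table 3: "Overall missing data rate", with no split by arm, visit or instrument.

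Table 1 schedules DASS-21, QLSCA, physical fitness and blood pressure at allocation, week 4 and week 8, and exempts neither arm. Section 2.4 makes one whole school the control group, with no intervention.

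**The concern.** These are the primary outcomes of a feasibility randomised trial, and section 2.2 looks ahead to a main trial. Three things look wrong in the printed text.

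1. The same 70% recruitment threshold is attached to two different populations.
2. Retention is counted in one arm only. The control arm is a separate school that receives nothing, so its follow-up cannot be inferred from TABATA completion. The only criterion that could register control loss is the overall missing-data rate, which pools it with everything else.
3. A count cannot be compared with a percentage, and the section on adherence names other measures.

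If this stands, the verdict on a primary outcome can depend on which passage is applied after the data are in. The study could also be called successful with poor control follow-up. Any between-arm comparison of the change scores in Table 4 needs post-intervention data from both schools, and section 2.9 rules out filling in missing values.

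**Working it through.** The thresholds are set rather than derived, so there is no figure in the plan to reproduce. The check is whether the same data can pass and fail.

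**Inputs.** Thresholds of 70%, 80%, 70% and 10% (Table 3); 8 weeks × 3 sessions = 24 sessions (section 2.5.1); three assessment times (Table 1); 25 per arm, which lies within both the 25–30 of section 2.2 and the 20–30 of section 2.9. The numbers eligible, lost and attending are assumptions chosen to illustrate.

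**Recruitment.** Table 3 is read as consenting / eligible over both schools, and section 2.9 as the same ratio in the TABATA school.

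| Eligible (TABATA, control) | Consenting in each | TABATA only (2.9) | Both schools (Table 3) |
|---|---|---|---|
| 36, 33 | 25 | 25/36 = 69.4%, fail | 50/69 = 72.5%, pass |
| 30, 45 | 25 | 25/30 = 83.3%, pass | 50/75 = 66.7%, fail |

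The verdict can reverse in either direction.

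**Retention and missing data.** Suppose TABATA loses 4 of 25 and control loses 10 of 25. TABATA retention is 21/25 = 84%, a pass. Control loss at week 8 is 10/25 = 40%, which no criterion measures. The overall missing rate depends on a denominator and a timing that the article does not fix:

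| Reading | Missing / planned participant-visits | Verdict at <10% |
|---|---|---|
| Three visits, all losses after week 4 | 14 / (2 × 25 × 3) = 14/150 = 9.3% | pass |
| Pre and post visits only | 14 / (2 × 25 × 2) = 14/100 = 14% | fail |
| Three visits, students leave before week 4 | 28/150 = 18.7% | fail |

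At 30 per arm with 5 and 12 lost, the first reading gives 17/180 = 9.4%, again a pass with 12/30 = 40% of control week-8 data gone.

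With TABATA at its minimum pass (21/25), the largest control loss that still satisfies the overall rule is:

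- losses after week 4, three visits: 10 of 25 (60% retained)
- pre and post visits only: 5 of 25 (80% retained), since (4 + 5)/100 = 9%
- losses before week 4, three visits: 3 of 25 (88% retained), since 2 × (4 + 3)/150 = 9.3%

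**Adherence.** Taking 24 sessions as the denominator, more than 70% means at least 17 sessions (17/24 = 70.8%; 16/24 = 66.7%). Even then the criterion is not fixed:

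- Suppose 15 of 25 students attend 24 sessions and 10 attend 7. Mean attendance is (15 × 24 + 10 × 7)/(25 × 24) = 430/600 = 71.7%, a pass. The share of students above 70% is 15/25 = 60%, a fail.
- Suppose 21 students complete with 18 sessions each and 4 drop-outs attend 6 each. Over all allocated, attendance is (21 × 18 + 4 × 6)/600 = 402/600 = 67%, a fail. Over completers alone it is 18/24 = 75%, a pass. The article does not state the completers-only reading, but nothing in it excludes that reading.

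**The case against.** The primary objective is the feasibility and acceptability of the TABATA module, so completion in the TABATA group is a proper primary outcome. That stands, and it should be kept.

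On recruitment, the Discussion repeats the 70% threshold without restricting it to TABATA, which favours the Table 3 reading. It does not remove the restriction in section 2.9.

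On adherence, the row is labelled a rate, attendance sheets are planned, and 24 sessions follow from the schedule, so sessions attended out of 24 is the natural reading. That is fair. The printed definition is nevertheless a count, and section 2.6 points to other measures without saying which one is judged against 70%.

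On missing data, the denominator is a detail that an article may leave to the full protocol or analysis plan. That also stands: by itself the absent denominator would be no finding. It matters here because the overall rate is the only criterion through which control loss could show.

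A reader might infer that Table 3 ignores the control arm altogether. The documents do not support that. Recruitment in Table 3 and the overall missing rate both include controls, section 2.9 sets a recruitment count for each group, and adherence cannot apply to an untreated arm. Only retention leaves controls out.

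**Conclusion.** The point holds in this form. The recruitment criterion contradicts itself between Table 3 and section 2.9. Adherence is a count set against a percentage and is quantified differently in section 2.6. No criterion measures control-arm retention in either place. The recruitment and adherence examples show that the verdict can change with the reading.

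The masking of control loss is possible but not general. The example with 40% of control week-8 data gone and 9.3% missing overall rests on participant-visits as the unit, three visits, and all losses after week 4. Under the other two readings the same losses fail the 10% limit. It would be wrong to conclude that the pooled rate hides control loss as a rule.

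A reader might also take the thresholds as go/no-go rules for the main trial. The article calls them success thresholds and feasibility goals and states no progression rule. The analysis is descriptive with confidence intervals. What is at stake is therefore the declared success or failure of the primary outcomes.

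**What to change.** Amend Table 3 and bring sections 2.6 and 2.9 into line with it:

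- **Recruitment:** one definition in both places, consented / eligible over both schools, also shown by school.
- **Retention:** keep TABATA completion at >80%. Add week-8 assessment completed / allocated in each arm, judged against the same >80%.
- **Adherence:** sessions attended / 24 scheduled, over all students allocated to TABATA, with sessions after withdrawal counted as missed. Report sets completed beside it.
- **Missing data:** keep the overall <10% criterion across all instruments, state its denominator, and report it by arm and visit. A separate <10% limit per arm on a week-8 score is not needed: it would require more than 90% of those scores and so make >80% follow-up on the same score redundant.

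The cost is wording and a few more tabulations of data already planned. The reported rates may look less favourable. The definitions should be fixed before results are seen.

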### Sample size

2.2

According to Whitehead et al. (2016) recommendations for pilot study sample sizes, to ensure the subsequent main trial achieves 90% power and a two-tailed 5% significance level, the sample size for each group in the pilot study should be set based on the expected effect size: a very small effect (0.1) corresponds to 75 participants, a small effect (0.2) to 25 participants, a medium effect (0.5) to 15 participants, and a large effect (0.8) to 10 participants. Furthermore, Dworkin (2012) noted in theory-based qualitative research that a sample size of 25–30 participants is typically required to achieve theoretical saturation and information redundancy. Integrating these recommendations from both statistical and qualitative research, this study sets the sample size per group at 25–30 participants. This aims to ensure sufficient statistical power while adequately capturing key experiences and feedback during the intervention process.

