Participants in the intervention group will undergo 8 weeks of TABATA training, while those in the control group will not receive any intervention or participate in any interviews. Table 1 outlines the participant recruitment timeline, key milestones, and scheduled assessment activities. Stage 2 will involve the qualitative phase of the study. Participants for this phase will be selected from the intervention group in Stage 1. Individual interviews will be conducted with a subset of students who received the intervention, as well as with PE teachers who delivered the training. The aim of this phase is to evaluate the feasibility and acceptability of the TABATA training module.

**Table 1 tab1:** SPIRIT (Standard Protocol Items: Recommendations for Interventional Trials) schedule of enrolment, interventions, and assessment.

Timepoint	Study period										
	Enrolment	Allocation	Post-allocation								Close-out
	9/2025–10/2025	9/2025–10/2025	Week 1	Week 2	Week 3	Week 4	Week 5	Week 6	Week 7	Week 8	12/2025
Enrolment											
Screening	✓										
Eligibility screen	✓										
Informed consent	✓										
Allocation		✓									
Interventions											
Intervention A											
Control											
Assessments											
DASS-21 Chinese version		✓				✓				✓	
Quality of life scale for children and adolescents (QLSCA) Chinese version		✓				✓				✓	
Physical fitness performance		✓				✓				✓	
Blood pressure		✓				✓				✓	

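### Retention is counted in the TABATA arm only and missing data is one overall rate, so no success criterion tests whether the control school is assessed at Week 8

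*Protocol article*

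**What the plan says.** Table 3 (section 2.7) lists four primary outcomes with success thresholds, and section 2.9 restates them as goals.

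- **Retention, >80%.** Table 3 defines it as "Proportion of students that in the TABATA training group complete the 8-week intervention". Section 2.9 agrees: "ensuring that more than 80% of students in the TABATA training group complete the 8-week intervention". The Discussion gives the threshold without naming an arm, but it does not change the definition.
- **Missing data, <10%.** Table 3 defines it only as "Overall missing data rate". Section 2.9 speaks of "maintaining an overall missing data rate of less than 10"%. Neither place states a denominator or a limit by arm, visit or instrument.
- **Adherence, >70%.** This counts sessions attended, so it can apply only to the trained arm.
- **Recruitment, >70%.** This is settled at entry, and section 2.9 ties the goal to the TABATA group.

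Table 1 schedules the "DASS-21 Chinese version", the quality-of-life scale, fitness and blood pressure at allocation, Week 4 and Week 8. Table 4 defines stress, quality of life and fitness as changes from before to after the intervention. On missing values, section 2.9 says "we will not use data interpolation to address any missing data".

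**The concern.** Once students are enrolled, the missing-data rate is the only criterion that can reach the control arm. If it pools the two arms, a complete TABATA arm dilutes loss at the control school. If it also pools visits, a complete baseline dilutes it further.

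The design makes this matter. Each arm is one school (section 2.4), so a local problem at one school falls wholly on one arm. A student without a Week 8 value has no change score, and the plan will not fill the value in. Section 2.9 gives the main purpose of the study as finding out whether the data can be collected. The stated success rule could be met while endpoint collection in the control arm fails, and the later main trial would depend on that collection.

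**Working it through.** The 10% and 80% limits are set by decision, so the plan has no derived figure to reproduce. The check counts how much control loss the limits allow.

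**Inputs from the protocol article**
- Missing data strictly below 10% (Table 3, section 2.9).
- Group size: "this study sets the sample size per group at 25–30 participants" (section 2.2). Section 2.9 has a wider range: "the intervention group and the control group will each recruit 20 to 30 participants". The main figures use 25.
- Three assessments per student (Table 1).

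**Assumptions not in the article**
- The denominator, for which three readings are shown.
- A missed visit means that all its instruments are missing.
- At first, the TABATA arm is complete, so all missing visits are control visits.

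**Formulas.** With n students per arm and v visits counted, S = 2 × n × v, and m is the largest whole number below 0.10 × S. Control Week 8 loss is m/n if only Week 8 is missed. On the three-visit base, if Weeks 4 and 8 are both missed, it is (m/2, rounded down)/n.

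**Results at n = 25**

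| Base for the overall rate | S | m | Only Week 8 missed | Weeks 4 and 8 missed |
|---|---|---|---|---|
| Week 8 only, or per participant | 50 | 4 (8.0%) | 4/25 = 16% | n/a |
| Baseline and Week 8 | 100 | 9 (9.0%) | 9/25 = 36% | n/a |
| All three visits | 150 | 14 (9.3%) | 14/25 = 56% | 7/25 = 28% |

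**Other group sizes, bases in the same order**
- n = 20: 3/20 = 15%; 7/20 = 35%; 11/20 = 55%, or 5/20 = 25% if Week 4 is also missed.
- n = 30: 5/30 = 16.7%; 11/30 = 36.7%; 17/30 = 56.7%, or 8/30 = 26.7% if Week 4 is also missed.

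**Counting items instead of visits, n = 25.** Four instruments at three visits plus two examinations give 14 items per student, so S = 2 × 25 × 14 = 700 and m = 69. Missing Week 8 costs 5 items (four instruments and the final examination): 69/5 rounds down to 13, and 13/25 = 52%. Missing Weeks 4 and 8 costs 9 items: 69/9 rounds down to 7, and 7/25 = 28%.

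**TABATA arm incomplete, n = 25.** Retention above 80% requires at least 21 of 25, so 4 may be lost (84% retained). Suppose they miss the same visits as the control students who are lost.
- Three visits, only Week 8 missed: 14 − 4 = 10, and 10/25 = 40%.
- Three visits, Weeks 4 and 8 missed: (14 − 8)/2 = 3, and 3/25 = 12%.
- Baseline and Week 8: 9 − 4 = 5, and 5/25 = 20%.
- Week 8 only: 4 − 4 = 0, so no control loss is allowed.

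**For comparison.** The same 10% limit applied within the control arm at Week 8 allows fewer than 2.5 of 25 students, so 2/25 = 8%.

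**The case against.** The strongest reply is that the largest figures rest on a denominator the article does not give, and a fuller protocol or analysis plan may define it. On a Week 8 or per-participant base, control loss cannot exceed 16% at 25 per arm. At least 84% of controls would then be assessed, which is within what the plan accepts as TABATA retention. The figures also shrink once the TABATA arm has losses of its own. Further, the primary objective is the feasibility of the TABATA module, so a retention criterion for that arm is sensible. Nothing stops the team from reporting missing data by arm in a descriptive analysis.

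Much of this stands, and it bounds the size of the problem. It does not remove the gap. The success thresholds are fixed in this article, and none of them covers control follow-up. A table by arm would show the loss but would not change whether the study is declared feasible.

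Two stronger readings are tempting, and the documents do not support them.
- A reader might infer that >80% retention and <10% missing data contradict each other. They do not. With a complete control arm, four TABATA leavers out of 25 give 4/150 = 2.7% or 8/150 = 5.3% missing visits, both under 10%. The criteria also measure different things, since a student who stops training can still be assessed.
- A reader might infer that an untreated control school is where loss is most likely. The article gives no attrition figures, screening takes place in school classes, and loss from a demanding exercise arm is no less plausible.

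**Conclusion.** The point holds as a gap in the success criteria. No criterion tests whether control students are assessed at Week 8, and the one overall rate does not do so on any base examined when the TABATA arm is complete. At 25 per arm, the allowed control loss at Week 8 is then 16%, 36%, or 28% to 56%, depending on the base and on whether Week 4 is also missed. All of these exceed the plan's own 10% limit.

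These are worst cases, not forecasts. They assume that whole visits are missed and that all loss is at the control school. A reader might take 28% to 56% as what the plan plainly permits; that holds only on the three-visit base with no TABATA loss. With 4 of 25 TABATA students also lost in the same pattern, that range becomes 12% to 40%. The change is worth making because it is cheap and bears on the study's stated purpose, but the point does not undermine the design.

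**What to change.** In Table 3, section 2.9 and the Discussion:

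1. Apply the missing-data criterion at Week 8, separately in each arm, across all the scheduled instruments, and state the denominator.
2. Add the proportion of control students assessed at Week 8 as a follow-up rate, for example with the >80% limit already used for TABATA retention.
3. Keep the overall missing-data rate as a description.

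The two limits should be set together. If students who are not assessed count as missing, a 10% limit within an arm allows 2 of 25 to be lost, while a follow-up limit of >80% allows 4 of 25. The text should say whether the missing-data rate is taken over all enrolled students or only over those assessed.

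The cost is wording in three places. No new data or visits are needed. The criterion becomes somewhat harder to meet.
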